### Resting metabolic rate

Resting metabolic rate will be measured using indirect calorimetry via a ventilated hood at baseline and end of the program. Participants will be instructed to be rested and fasted for a minimum of 12 hours prior to the measurement of resting metabolic rate and will be tested while lying down in an environmental chamber with an ambient temperature of 24° C and relative humidity of 60%
[26]. After a 15-minute equilibration period, respiratory gas will be collected for 30 minutes using a ventilated hood. Minute ventilation (volume of air inhaled and exhaled in one minute), O_2_ and CO_2_ content will be analysed using a Parvomedics TrueOne 2400 analyser (Parvomedics, Sandy, UT). Resting metabolic rate will be defined as the lowest 5-minute average obtained during the 30-minute measurement period
[26]. The TrueOne analyser system has demonstrated reliability and validity, with a within-subject coefficient of variation of 5.4% and comparable results to other validated measures of resting metabolic rate
[27].

### Accelerometry

Accelerometry will be used to objectively assess the physical activity of participants at all measurement points using the Actigraph GT3X (Actigraph, Penascola, FL). Participants will be required to wear the accelerometer on an elastic waist belt aligned with the right anterior axillary line for seven days at each measurement period at all times (including sleep), except when showering, bathing, swimming or engaging in contact sports. Participants will be asked to complete a brief log to record whether and when they removed the monitor for any reason. Accelerometers will be set to capture 30 second epochs and minimum wear time will be defined as 10 hours per day for four of the seven days, one of which must be a weekend day. Non-wear time will be defined as 60 minutes of consecutive zeros. Total counts and minutes spent in sedentary, light, moderate and vigorous physical activity domains according to the vertical axis will be calculated using the Actlife 5.5 software (Actigraph, Penascola, FL) using cut-offs previously described by Troiano and colleagues
[28].

The Actigraph has demonstrated inter-device reliability (r=0.98)
[29] and validity against indirect calorimetry when worn on the hip (r=0.56, p<0.001)
[30] in assessing activity in adult populations. In a recent comparison of four accelerometers assessing standardised bouts of treadmill walking across multiple trials, the Actigraph was found to have the least variability across accelerometers and the highest overall reliability
[31].

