At each time point, the MARCA will be administered on two occasions, each time recalling two consecutive days, which must include one weekend day and one weekday (such as Friday and Saturday) resulting in a total of four recalled days at each measurement period. For analyses, the four recall days will be averaged using a 5:2 weighting for weekdays: weekend days. Moderate to vigorous physical activity minutes will be calculated as the average number of minutes spent in activities expected to elicit ≥3 METs according to the MARCA compendium. Physical activity level (PAL, in METs) will be calculated using the factorial method, that is by multiplying the rate of energy expenditure associated with each activity (in METs) by the number of minutes for which that activity was performed, summing them across the day, and dividing by 1440 (minutes per day). To determine time spent in zones of energy expenditure, minutes spent in five mutually exclusive and exhaustive energy expenditure zones: 0.0-0.9 METs (sleep); 1.0-1.9 METs (very light physical activity, VLPA); 2.0-2.9 METs (light physical activity, LPA); 3.0-5.9 METs (moderate physical activity, MPA); and ≥6 METs (vigorous physical activity, VPA) will be calculated. Finally, to determine a time use profile, minutes spent in major “activity sets” will be determined, including Physical Activity, Computer, Active Transport, Passive Transport, Quiet Time, Self-Care, Socio-cultural, Work/Study, Chores, Sleep, and TV/Videogames.

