### Statistical analysis

As this study is aiming to address a mechanism rather than test the effectiveness of the exercise intervention, analysis will be carried out on a per protocol basis where only those participants who complete the intervention will be included in the analyses. Subsequent analyses will also be carried out based on 50% and 75% compliance thresholds with the prescribed volume of physical activity according to objectively monitored adherence (based on heart rate monitoring).

Socio-demographic and anthropometric data will be analysed descriptively. Baseline characteristics of the three groups will be presented but not formally tested for differences. Random effects mixed modelling will be used with time (0, 3, 6, 12 and 24 weeks) and group allocation (*Control, Moderate, Extensive)* as the fixed factors. A time by group interaction term will be used to formally test the differences between the groups. Alpha will be set at 0.05. The response variables for the primary analysis investigating the activitystat hypothesis will be total and activity energy expenditure derived from doubly labeled water, resting metabolic rate derived from indirect calorimetry, total counts and minutes spent in sedentary, light and MVPA derived from accelerometry and minutes spent in MVPA, physical activity superdomain and physical activity level derived from the MARCA.

Response variables for secondary analyses will include use of time derived from the MARCA to determine how participants adjust their daily activity patterns when commencing an exercise program and anthropometric (height, mass, girths, skin folds, volumes) and physiological variables (blood pressure, fasting blood glucose and total serum cholesterol, VO_2max_) to investigate dose response relationships between physical activity and anthropometric and physiological variables.

A priori power calculations determined that a sample of 26 participants per group (n=78) should be able to detect small to moderate effect sizes (Cohen’s d=0.2-0.6) for within groups (time effect) and group x time interactions, at 5% alpha level and 80% power. Due to documented dropout rates of physical activity interventions
[4] and the intensive assessment protocol for this study, a dropout rate of 25% will be anticipated and therefore a total of 46 participants per group (n=138) will be recruited.

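### The accelerometer is worn through sleep, but the stated scoring rules do not separate sleep from waking time, so sedentary minutes partly reflect how restless the sleep was

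*Protocol article*

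**What the plan says.** The Accelerometry section of the protocol article asks participants to wear the monitor for seven days at each measurement period, "at all times (including sleep), except when showering, bathing, swimming or engaging in contact sports". The rules for processing the data are then given:

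- Valid data: "minimum wear time will be defined as 10 hours per day for four of the seven days", with at least one weekend day. The hours are not limited to waking time.
- Non-wear: "Non-wear time will be defined as 60 minutes of consecutive zeros".
- Log: participants "complete a brief log to record whether and when they removed the monitor for any reason". Bed and wake times are not mentioned.
- Scoring: "Total counts and minutes spent in sedentary, light, moderate and vigorous physical activity domains according to the vertical axis", by published count cut-offs. There is no sleep category.

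The Statistical analysis section lists "total counts and minutes spent in sedentary, light and MVPA derived from accelerometry" among the response variables of the primary analysis. Sleep has its own energy-expenditure zone in the use-of-time recall (MARCA), but nothing links the recall to the scoring of the accelerometer.

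**The concern.** The wear instruction and the scoring rules do not fit together. A minute of sleep with the monitor on can be treated in two ways. If it lies in a run of at least an hour without counts, it is removed as non-wear, although the monitor was worn. If a small movement breaks the run, it stays as wear and falls in the lowest count class, sedentary. Neither is correct, and the split between the two depends on how often the sleeper moves.

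Sedentary time is a natural place to look for compensation: if imposed exercise is offset elsewhere, more sitting is one obvious form. A sedentary measure that moves with sleep restlessness is a weak instrument for that question. The same rules let sleep count towards the 10 hours, so accepted days may differ widely in waking wear. Total counts and all the minute categories depend on waking wear.

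**Working it through.** The plan gives no figure that rests on these rules, so there is nothing of its own to reproduce. The checks below show how much the rules could matter.

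**Inputs from the document.** Valid day 10 h; non-wear 60 min of zeros; imposed load about 150 (Moderate) and 300 (Extensive) min/week (Intervention section).

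**Assumptions, not in the document.** Sleep of 8 h (480 min), with 6-9 h as the range; rate of movement in sleep; count rate in sleep relative to waking; size of any change between visits.

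**1. Yardstick.** Imposed load per day: 150/7 = 21.4 min and 300/7 = 42.9 min.

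**2. Shift of sleep between wear and non-wear.** For 8 h of sleep, 5% is 0.05 × 480 = 24 min/day and 10% is 0.10 × 480 = 48 min/day. For 6 h (360 min) the figures are 18 and 36; for 9 h (540 min) they are 27 and 54. A small reclassification of sleep is thus of the same order as the imposed load.

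**3. How the 60-minute rule splits a night.** Movements were simulated as a Poisson process over a 480-minute night, 4,000 nights per rate. Gaps of 60 minutes or more were scored as non-wear and the rest as wear, hence sedentary.

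| Movements per hour (assumed) | Mean sleep minutes scored sedentary | SD between nights |
|---|---|---|
| 0.25 | 24 | 33 |
| 0.5 | 62 | 54 |
| 1 | 147 | 80 |
| 2 | 300 | 90 |
| 4 | 441 | 52 |
| 6 | 472 | 24 |

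The result runs from almost none of the night to almost all of it. Going from 0.5 to 1 movement per hour adds 147 − 62 = 85 min.

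**4. Valid days.** Waking wear needed = 10 h minus sleep scored as wear. If all sleep is so scored, that is 4, 3, 2 or 1 h for 6, 7, 8 or 9 h of sleep. With 8 h of sleep an accepted day could hold 2 to 16 h of waking wear (16/2 = 8-fold). With the rule applied to waking time it would hold 10 to 16 h (16/10 = 1.6-fold). The lower end of 2 h is a bound, not an expectation.

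**5. Total counts.** If the count rate in sleep is a fraction f of the waking rate, the share of the 24-hour total due to sleep is 8f/(16 + 8f). For f = 0.01 this is 0.08/16.08 = 0.5%; for f = 0.05 it is 0.4/16.4 = 2.4%. Sleep itself adds little. Waking wear matters more: at a constant waking rate, 14 h instead of 16 h gives 14/16 = 87.5% of the counts, a fall of 12.5% with no change in behaviour if counts are not scaled.

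**The case against.** The strongest reply is that a journal article condenses. It does not say that sleep is kept in sedentary minutes or that counts are left unscaled, and a fuller protocol or analysis plan may contain a sleep filter. This stands in part. A reader might infer that the article prescribes a raw, unscaled sum of counts; it does not, and is only silent on adjustment. The wear instruction, the 10-hour rule, the zero rule and the classes are stated, however, and they do not fit round-the-clock wear. A sleep filter elsewhere would have to alter them.

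Second, a reader might infer that sleep contaminates total counts as it does sedentary minutes. It does not: the direct share is about 0.5-2.4% under the assumed rates, and MVPA minutes gain little or nothing from sleep. What remains for these is dependence on waking wear.

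Third, a reader might infer a bias between the arms. The document does not show one. Arms are randomised, all follow the same wear instruction, and the test is group by time, so a sleep component that changes alike in all arms cancels on average and leaves noise.

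Fourth, there are partial safeguards. The removal log could show that a long run of zeros was worn time. But restoring those minutes without identifying sleep would only move still sleep into the sedentary class. The MARCA would reveal a change in sleep by arm, but covers four recalled days per period against seven days of wear. Several other primary-analysis responses, including the doubly labeled water, resting metabolic rate and MARCA measures, do not depend on these rules.

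**Conclusion.** The point holds for accelerometer sedentary minutes: the stated rules, followed exactly, mix an arbitrary part of sleep into a primary-analysis response and delete the rest as non-wear. It holds in a weaker form for total counts, which depend on waking wear without a stated adjustment, and for the validity rule, which sleep can help to satisfy.

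The size is a range that rests on assumptions. With 8 h of sleep, a 5-10% reclassification is about as large as the imposed daily load. Sleep length, movement rates and changes between visits are not in the document, so no estimate of the actual error is possible. The expected consequence is added noise; bias in the group-by-time test arises only if sleep or wear changes differently by arm, and its direction cannot be derived. The matter should be corrected because the remedy is cheap, but it does not undermine the trial's energy-expenditure outcomes.

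**What to change.** In the Accelerometry section:

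1. Identify and remove sleep before any other step, using bed and wake times added to the existing removal log, or a sleep algorithm fixed in advance.
2. Apply the 10-hour minimum and the 60-minute-zero rule to waking time only, and use the removal log when deciding on non-wear.
3. Define sedentary minutes as minutes of waking wear below the cut-off.
4. Analyse counts per minute of waking wear, or adjust for waking wear time in the model.

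The cost is rule wording, one more line for participants to fill in, and the loss of some days that now qualify with the help of sleep.

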### Multimedia activity recall for children and adults

Use of time will be measured via telephone interview using the Multimedia Activity Recall for Children and Adults (MARCA). The MARCA is a computerised 24-hour recall tool and will be administered at all measurement points of the study. The MARCA asks participants to recall their previous day from midnight to midnight using meal times as anchor points in a segmented day format. Participants recall their day in time slices of five minutes or more by choosing from 520 different activities organised under a number of categories, such as “Self-Care”, “Occupation” or “Sport/Recreation”. Each activity in the MARCA is assigned a metabolic equivalents (METs) value based on an expanded version of the Ainsworth compendium so that energy expenditure can be estimated
[32,33].

Originally designed for use in children and adolescents
[34], the MARCA has been modified for use in adults
[35]. The adult version of the MARCA has test-retest reliabilities in adults of 0.990-0.997 (p≤0.0001) for MVPA, physical activity level (PAL; average daily rate of energy expenditure in METs), sleep and screen time, and convergent validity between physical activity level (estimated average rate of energy expenditure) and accelerometer counts/minute of rho = 0.72
[35]. A recent comparison with the gold standard doubly labeled water showed correlations of rho = 0.70 for total daily energy expenditure (Foley et al. 2012).

At each time point, the MARCA will be administered on two occasions, each time recalling two consecutive days, which must include one weekend day and one weekday (such as Friday and Saturday) resulting in a total of four recalled days at each measurement period. For analyses, the four recall days will be averaged using a 5:2 weighting for weekdays: weekend days. Moderate to vigorous physical activity minutes will be calculated as the average number of minutes spent in activities expected to elicit ≥3 METs according to the MARCA compendium. Physical activity level (PAL, in METs) will be calculated using the factorial method, that is by multiplying the rate of energy expenditure associated with each activity (in METs) by the number of minutes for which that activity was performed, summing them across the day, and dividing by 1440 (minutes per day). To determine time spent in zones of energy expenditure, minutes spent in five mutually exclusive and exhaustive energy expenditure zones: 0.0-0.9 METs (sleep); 1.0-1.9 METs (very light physical activity, VLPA); 2.0-2.9 METs (light physical activity, LPA); 3.0-5.9 METs (moderate physical activity, MPA); and ≥6 METs (vigorous physical activity, VPA) will be calculated. Finally, to determine a time use profile, minutes spent in major “activity sets” will be determined, including Physical Activity, Computer, Active Transport, Passive Transport, Quiet Time, Self-Care, Socio-cultural, Work/Study, Chores, Sleep, and TV/Videogames.

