### Intervention

The two intervention conditions are based upon a six week group-based physical activity intervention - a program previously developed and tested within the University of South Australia, known as the 40-DAY Physical Activity Program
[18]. The program comprises both group-based, instructor-led and self-directed individual exercise sessions with progressive increases in exercise intensity. The two intervention conditions involve similar types of physical activities and intensities, and differ only in volume. The group sessions are graded in intensity and are designed to expend approximately 800 kJ in the first week and to increase by about 200 kJ per session in each subsequent week.

This intervention was designed within the framework of several theoretical components important for long-term behavioural change, including an intra-personal focus on self-efficacy, outcome expectancy of health and fitness benefits, inter-personal and cultural factors (group work), physical activity monitoring, goal setting, identifying barriers and enablers and health and fitness testing
[18]. An expanded explanation of the methodological considerations of the intervention design is available in the paper by Norton and colleagues
[18].

The Moderate intervention is designed to involve approximately half the load of the Extensive group. Participants in the Moderate group will attend instructor-led group classes of 60 minutes duration three times per fortnight. Participants will then be required to carry out a minimum of 30 minutes of self-directed activities on a further two days per week. The Moderate exercise intervention is designed to increase MVPA by approximately 150 minutes per week (equivalent to approximately 4000 kJ/week). This dosage is consistent with the minimum level of energy expenditure recommended for exercise beginners by the United States Surgeon General (600 kJ/day)
[19]*.* Table
1 shows the activities and the progressive increase in planned energy expenditure during the intervention for the Moderate group.

**Table 1 T1:** Moderate group physical activity itinerary (grey shading indicates group exercise session)

	**Sunday**	**Monday**	**Tuesday**	**Wednesday**	**Thursday**	**Friday**	**Saturday**
**Week 1 600 kJ/session**					Introductory circuit involving stretching and body awareness activities such as climbing, rolling, balancing, hopping, using a range of different surfaces.	Individual exercise session	Individual exercise session

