**Week 2 700 kJ/session**			Training circuit with light hand-held weights, step-ups, stair climbing (one flight), fit ball and core stability exercises.	Individual exercise session	Circuit training including light resistance with dumbbells and medicine ball activities, dynamic stretching activities, introduction to boxing and skipping.		Individual exercise session
**Week 3 800 kJ/session**		Individual exercise session	Resistance class with hand-held dumbbells or light barbells (<10kg), dynamic stretching, resistance routines.		Outdoor circuit training including walking with hand-held weights, stair and hill climbing and introduction to jogging.		Individual exercise session
**Week 4 900 kJ/session**			Circuit training including dynamic stretching activities, resistance activities, spin class, boxing.		Individual exercise session		Kayaking in two-person sit-on-top kayaks ~1.5 hours’ duration
**Week 5 1000 kJ/session**		Individual exercise session	Outdoor team games- modified soccer or lacrosse.		Circuit training including dynamic stretching activities, resistance activities, jogging or stair climbing, spin class.		Individual exercise session
**Week 6** **1200 kJ/session**	Group bush walk ~1.5-2 hours duration	Individual exercise session			Sand dune and beach activities: walking or jogging through sand hills, team games on beach.		

Participants in the Extensive group will attend instructor-led group classes of 60 minutes duration three times per week. Participants will then be required to carry out a minimum of 30 minutes of self-directed activities on a further four days per week. The extensive exercise intervention is designed to increase MVPA by approximately 300 minutes per week (equivalent to approximately 8000 kJ/week). Overall, participants will be required to complete at least 30 minutes of activity every day for 40 days. Table
2 shows the activities and the progressive increase in planned energy expenditure during the intervention for the Extensive group. To reflect the modified nature of the 40-day program in this study for the Moderate exercise group, the intervention conditions will now be referred to as the UniSA Physical Activity (PA) program.

**Table 2 T2:** Extensive group physical activity itinerary (grey shading indicates group exercise session)

	**Sunday**	**Monday**	**Tuesday**	**Wednesday**	**Thursday**	**Friday**	**Saturday**

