**Week 1 600 kJ/session**		Introductory circuit involving stretching and body awareness activities such as climbing, rolling, balancing, hopping, using a range of different surfaces.	Individual exercise session	Circuit training including light resistance with dumbbells and medicine ball partner activities, dynamic stretching activities, introduction to step-ups.	Individual exercise session	Training circuit with hand held weights, step-ups, stair climbing (one flight), fit ball and core stability exercises.	Individual exercise session
**Week 2 800 kJ/session**	Individual exercise session	Aerobic activities: warm up, stretching exercises, aerobic activities increasing speed, cool down stretching.	Individual exercise session	Circuit training including light resistance with dumbbells and medicine ball activities, dynamic stretching activities, introduction to boxing and skipping.	Individual exercise session	Resistance class with hand-held dumbbells or light barbells (<10kg), dynamic stretching, resistance routines .	Individual exercise session
**Week 3 1000 kJ/session**	Individual exercise session	Outdoor circuit training including walking with hand-held weights, stair and hill climbing, introduction to jogging.	Individual exercise session	Circuit training including light resistance activities, dynamic stretching activities, introduction to spin class.	Individual exercise session	Aerobics class, warm-up, floor exercises o music, stretching and cool down activities.	Individual exercise session
**Week 4 1200 kJ/session**	Individual exercise session	Outdoor circuit training including walking with hand-held weights or jogging, stair climbing, boxing, skipping.	Individual exercise session	Outdoor team games – modified lacrosse.	Individual exercise session	Circuit training including dynamic stretching activities, resistance activities, jogging or stair climbing, spin class.	Kayaking in two-person sit-on-top kayaks ~1.5 hour duration
**Week 5 1400 kJ/session**	Individual exercise session	Outdoor team games – modified soccer.	Individual exercise session	Circuit training including dynamic stretching activities, resistance activities, jogging or stair climbing, spin class.	Individual exercise session	Circuit training including dynamic stretching activities, resistance activities, jogging or stair climbing, spin class.	Individual exercise session

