### Outcome measures

All participants will undergo a number of measurements at five time periods during the study: baseline or week zero (before the program begins), mid-program (weeks 3–4), end-program (week 5–6), and at 3 month and 6 month follow-up. These measurements will include doubly labeled water, resting metabolic rate, use of time recalls, accelerometry, various anthropometric and physiological measures and submaximal VO_2max_ tests. Figure
1 provides an overview of the outcome measures assessed at each time point. All outcome measures will be administered by trained, blinded research assistants.

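### The MARCA recall rule can sample only Friday and Monday as weekdays, so it misses every Moderate weekday class and over-counts the Extensive arm's classes

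*Protocol article*

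**What the plan says.** The Protocol article, section on the Multimedia Activity Recall for Children and Adults (MARCA), sets two recall occasions per time point, "each time recalling two consecutive days, which must include one weekend day and one weekday (such as Friday and Saturday"). Two weekdays and two weekend days are thus collected each time. The section adds that "the four recall days will be averaged using a 5:2 weighting for weekdays: weekend days". The Outcome measures section places the two in-program measurements at "mid-program (weeks 3–4), end-program (week 5–6").

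The Intervention section fixes the class days:

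- **Moderate arm:** the prose gives "instructor-led group classes of 60 minutes duration three times per fortnight" plus at least 30 minutes on two further days a week. In Table 1 all nine weekday classes are on Tuesday or Thursday, for example the week 5 Tuesday class, "Outdoor team games- modified soccer or lacrosse". Two further group sessions fall at weekends: kayaking on the Saturday of week 4 and a bush walk on the Sunday of week 6.
- **Extensive arm:** three 60-minute classes and four self-directed days a week. In Table 2 the classes are on Monday, Wednesday and Friday of every week, for example the week 3 Friday class, "Aerobics class, warm-up, floor exercises".

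The Statistical analysis section lists MARCA minutes of MVPA, "physical activity superdomain and physical activity level derived from the MARCA" among the response variables of the primary analysis, tested by the time-by-group interaction. MARCA use of time also serves the secondary aim on how participants rearrange their day.

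**The concern.** A pair of consecutive days with one weekday and one weekend day must straddle one end of the weekend. Tuesday, Wednesday and Thursday can therefore never be recalled, and each recalled Friday or Monday counts for two and a half weekdays. That would matter less if exercise were spread alike over the week in all arms, but the timetables put it on different days. The rule looks past the Moderate arm's weekday classes and looks only at class days in the Extensive arm. The error is systematic and differs by arm, so neither randomisation nor a larger sample removes it.

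At stake is the in-program reading of the MARCA results. A shortfall in recorded activity against the imposed load is what compensation would look like. On average the rule produces such a shortfall in Moderate without any compensation, and in Extensive it adds a surplus that would cover real compensation. At mid-program the other primary-analysis check is accelerometry alone, because doubly labeled water and resting metabolic rate are measured only at baseline and end of program.

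**Working it through.** **1. Permitted pairs.** Of the seven consecutive-day pairs, Mon–Tue, Tue–Wed, Wed–Thu and Thu–Fri have no weekend day, and Sat–Sun has no weekday. Fri–Sat and Sun–Mon remain.

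**2. The plan's own loads.** Moderate: 1.5 × 60 + 2 × 30 = 150 min/week. Extensive: 3 × 60 + 4 × 30 = 300 min/week. Both match the Intervention section.

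**3. Inputs for the check.** Days come from Tables 1 and 2. Class 60 and individual session 30 minutes come from the prose, and kayaking 90 minutes from the tables. The bush walk is taken as 105 minutes, the middle of the stated 1.5–2 hours. Full adherence on the table days and no compensation are assumed.

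**4. Estimator.** Weekly minutes = 5 × mean(recalled weekdays) + 2 × mean(recalled weekend days). Each occasion supplies one of each, so the result for two occasions is the mean of their single-pair values. The average over all six ways of choosing two of the four pairs in a two-week window is the mean of the four values.

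| Week | Moderate Fri–Sat | Moderate Sun–Mon | Moderate scheduled | Extensive Fri–Sat | Extensive Sun–Mon | Extensive scheduled |
|---|---|---|---|---|---|---|
| 3 | 5×0+2×30 = 60 | 5×30+2×0 = 150 | 180 | 5×60+2×30 = 360 | 5×60+2×30 = 360 | 300 |
| 4 | 5×0+2×90 = 180 | 0 | 180 | 5×60+2×90 = 480 | 360 | 360 |
| 5 | 60 | 150 | 180 | 360 | 360 | 300 |
| 6 | 0 | 5×30+2×105 = 360 | 195 | 5×60+2×0 = 300 | 5×60+2×105 = 510 | 345 |

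**5. Averages (min/week).**

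- Weeks 3–4, Moderate: (60+150+180+0)/4 = 97.5 against 180, or −46%.
- Weeks 3–4, Extensive: (360+360+480+360)/4 = 390 against 330, or +18%.
- Weeks 5–6, Moderate: (60+150+0+360)/4 = 142.5 against 187.5, or −24%.
- Weeks 5–6, Extensive: (360+360+300+510)/4 = 382.5 against 322.5, or +19%.

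**6. Spread over single combinations.** Moderate runs from 30 to 165 min/week in weeks 3–4 and from 30 to 255 in weeks 5–6, where two of the six combinations (210 and 255) exceed the scheduled 187.5. Extensive runs from 360 to 420 and from 330 to 435. When both arms recall the same pairs, the Moderate share of its schedule is below the Extensive share in 11 of 12 combinations and about equal in the other (136% against 135%).

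**7. Sensitivity (recorded as % of scheduled).**

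| Assumption | Moderate wk 3–4 | Moderate wk 5–6 | Extensive wk 3–4 | Extensive wk 5–6 |
|---|---|---|---|---|
| Base case | 54 | 76 | 118 | 119 |
| Bush walk 90 / 120 min | 54 / 54 | 75 / 77 | 118 / 118 | 119 / 118 |
| 40 countable min per class | 97.5/150 = 65 | 142.5/157.5 = 90 | 290/270 = 107 | 282.5/262.5 = 108 |
| Moderate at prose class frequency | 97.5/150 = 65 | 142.5/157.5 = 90 | – | – |
| Both of the last two | 97.5/130 = 75 | 142.5/137.5 = 104 | 107 | 108 |

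The 40-minute row removes the 10-minute warm-up and 10-minute cool-down. Table 1 shows four group sessions in each of these two windows where the prose implies three. The prose-frequency row removes one unseen 60-minute class per window, or 30 min/week. The last row removes a further 40/2 = 20 min/week from the 40-minute case. Counting the Extensive week 6 stretching class as zero gives 307.5/292.5 = 105% in weeks 5–6.

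**The case against.** The strongest reply is that this is one self-report instrument at two of five time points. The abstract names doubly labeled water and accelerometry as the primary outcome measures and puts use of time among the secondary ones. Doubly labeled water runs over 14 days and accelerometry over seven, and neither uses this rule, so they could expose a MARCA artefact at end of program. No classes are timetabled at baseline or follow-up. This stands and limits the severity.

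The size is also fragile. It depends on how many minutes of a class reach 3 METs, on which pairs are drawn, and on Table 1 against the prose, which disagree on Moderate group sessions (11 against 9 over six weeks) and must be reconciled. Self-directed sessions may move to other days. The percentages are of session minutes, not of total MARCA MVPA or physical activity level. All of this stands too. If 40-minute counting and the prose frequency are combined, the Moderate shortfall in weeks 5–6 disappears (104%).

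A reader might infer that the artefact imitates a dose threshold. It does not. The Background section wants a stimulus strong enough to induce compensation, so a threshold means compensation at the larger load and not at the smaller. The average artefact runs the opposite way. A reader might also infer that Moderate group activity is never observed. That too goes beyond the tables: only the weekday classes are invisible, while the kayaking and the bush walk can be recalled.

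**Conclusion.** The concern holds for the in-program MARCA results and should be fixed. The recall rule read with the two timetables leaves no doubt about which days can be seen: none of the nine Moderate weekday classes, and only class days among the Extensive weekdays against a true three in five.

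Under the base assumptions the average error in session minutes is −46% and −24% for Moderate and +18% and +19% for Extensive. Varying one assumption at a time brings Moderate to about −35% and −10%, and Extensive to between +5% and +8%. The mid-program contrast between arms is the most robust part. The end-program Moderate shortfall is the least certain, for a single participant and on average.

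The consequence is that in-program MVPA, physical activity superdomain, physical activity level and use of time from the MARCA could hide or reverse a dose threshold. The documents do not support the wider inference that the trial's main test is invalid, because doubly labeled water, accelerometry, and MARCA at baseline and follow-up are untouched.

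**What to change.** Keep two calls, four recalled days and the 5:2 weighting, and change which days are recalled. At each time point, assign each participant at random, by the same scheme in all three arms, to one of five equally likely schedules:

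1. Sat–Sun plus Mon–Tue
2. Sat–Sun plus Tue–Wed
3. Sat–Sun plus Wed–Thu
4. Sat–Sun plus Thu–Fri
5. Fri–Sat plus Sun–Mon

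Each weekday appears in two of the five schedules, a 2/5 chance, and both weekend days appear in all of them, so the 5:2 average is unbiased in every arm. For Moderate week 3 the five weekday means are 45, 30, 30, 30 and 15. Their average is 30, and 5 × 30 + 2 × 15 = 180, the scheduled load. Spread the schedules evenly over the weeks of each measurement window. Drawing only from the four weekday pairs is not enough: it samples Tuesday to Thursday twice as often as Monday and Friday and leaves +11% in Moderate and −5% in Extensive for weeks 3–4.

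The cost is somewhat more complex call scheduling and more day-to-day variation between participants, with no extra calls or recalled days.

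If calls are already fixed, report the bias and do not read in-program MARCA contrasts between arms as evidence for or against compensation. Substituting heart-rate-monitor minutes is not a repair: controls do not wear the monitors, and swapping in session minutes breaks the 1440-minute day on which physical activity level rests.
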